## Exposure Codes

- PCV13 vaccination will be identified by the CPT code 90670 and the NDC codes 00005197101, 00005197102, 00005197104, 00005197105.
- PCV 7 vaccination will be identified by the NDC codes 00005197049, 00005197050, 00005197067, 54569511700.
- Unspecified PCV vaccine will be identified by HCPCS codes G0009, S0195 and the CPT code 90669. (The latter code is technically for PCV7, but we will treat it as “unspecified” PCV in order to guard against possible misclassification of PCV13 as PCV7.)

Unspecified PCV vaccine prior to February 24, 2010 will be assumed to be PCV7 and after August 2010 will be assumed to be PCV13 based on the date of approval for PCV13 and the fact that by July 2010, Pfizer reported that >90% of its private shipments of pneumococcal conjugate vaccines were for PCV13.[^11^](#_ENREF_11) Information related to unspecified PCV vaccines received between Feb 24 and Aug 31, 2010, will not be included in analyses. Data on all vaccinations occurring within the first two years of life will also be captured.

## Outcome Definition

Cases of Kawasaki disease will be identified by the ICD-9 code 446.1 and ICD-10 code M30.3 (acute febrile mucocutaneous lymph node syndrome) in the inpatient setting in any position (primary diagnosis, secondary diagnosis, etc.). We assume that a confirmed or suspected case of Kawasaki disease would be admitted to a hospital to initiate treatment or undergo further clinical evaluation. Only the first code in 365 days in the inpatient setting for patients at least 365 days of age or first ever for those under 365 days of age will be considered in order to exclude follow-up visits for Kawasaki disease.

## Risk Window

Risk windows will include 1-28 days following all doses of PCV13 vaccines. This is the same risk window that was used in the VSD evaluation of PCV13 vaccine and is supported by evidence that among siblings, more than one half of second Kawasaki disease cases in each family developed within 10 days of onset of symptoms in the first case.[^5^](#_ENREF_5)^,^[^25^](#_ENREF_25) We will evaluate diagnoses within 42 days following all doses of PCV13 vaccines in order to identify cases whose symptoms began within the 28 day risk window even if their diagnosis was not made or recorded until later. Cases will be classified as occurring in the risk or control window based on the day that symptoms began. The control window is discussed in the next section.

## Statistical AnalysEs

### Descriptive analysis

Descriptive analyses using automated claims data will be performed to characterize the PCV7 and PCV13 vaccination data and Kawasaki disease data. They will include frequency distributions of age at the time of receipt of the vaccines stratified by Data Partner, sex and year, and frequency distributions of the number of Kawasaki disease cases by age.

### Overview of hypothesis-testing analyses

A challenge in studying PCV13 and Kawasaki disease will be the confounding effect of age, as both vaccination and the risk of Kawasaki disease are age-dependent. To confront this challenge, we will use both a *self-controlled risk interval (SCRI)*[*^26^*](#_ENREF_26)*^,^*[*^27^*](#_ENREF_27) and a *cohort* design. A major advantage of the former, which we are pre-specifying as the primary method, is that it inherently controls for all fixed (non-time-varying) potential confounders such as gender, race/ethnicity, and chronic predisposing conditions, by virtue of each subject serving as his/her own control. Another advantage of the SCRI design is that it uses only exposed cases, thus minimizing potential misclassification bias due to incomplete data on vaccine exposure. A possible disadvantage is that adjustment for time-varying confounders such as age must be made explicitly, and estimation of the age effect may introduce error. The cohort design is likely to have higher statistical power than the self-controlled design, due to the relatively large amount of historical and concurrent unexposed data involved in the generation of expected counts. However, its ability to control for time-invariant confounding is not as good as that of the self-controlled approach. If there are differences among racial/ethnic groups in vaccine coverage and timing, an important potential confounder in the cohort design will be race/ethnicity. The point estimates are also subject to bias from misclassification of exposure if some vaccinations are not recorded in the claims data and not captured during the chart review process.

### Self-controlled analysis

We will use a self-controlled risk interval (SCRI) design with a risk interval of Days 1-28 post-vaccination and a 28-day-long comparison (control) interval following this risk interval (Figure 4). We will capture diagnoses that occur up to 14 days beyond the end of the control window in order to identify cases in which symptoms began within the control window. Cases will be classified as occurring in the risk or control window based on the day that symptoms began. The null hypothesis is that the risk of Kawasaki disease is the same during the 28 days after PCV13 vaccine as it is during the subsequent 28–day-long control period. Because the recommended interval between doses 1 and 2 and between doses 2 and 3 is 2 months, there is less time in which to position the control interval than for the subsequent doses. The control interval will be Days 29-56 following doses 1 and 2. For doses 3 and 4, it will be Days 43-70 post-vaccination (Figure 4). (The latter is preferable due to uncertainty about the true period of vaccine-associated risk, which, if it exists, might extend beyond 28 days after vaccination.) There will be no censoring of person-time within risk and control windows. Only individuals with an observation in either the risk or the control interval are informative for this self-controlled analysis. In the final report, we will provide the following descriptive information, summed over all Data Partners, but separate for each dose: (i) total number of cases in the risk interval, (ii) total number of cases in the control interval, and (iii) a histogram of the total number of cases by age in weeks at the time of vaccination.

Kawasaki disease

Dose 1 Kawasaki disease Dose 2 Dose 3 and 4

**1 28 29 56 1 28 29 56 1 28 43 70**

risk control risk control risk control

Figure 4. Self-controlled risk interval design to evaluate the incidence rate ratios comparing rates in risk vs. control intervals.

We will run both unadjusted and age adjusted analyses. The unadjusted analysis will use logistic regression. We will employ two methods for adjustment of age.

Our primary analysis will use risk-by-age estimates from the literature to estimate the risk of Kawasaki disease by week of age. Specifically, we will use the smoothed estimates from Holman et al.’s data on hospitalizations for Kawasaki Syndrome in the United States.[^24^](#_ENREF_24) With such an external estimate, age enters the regression through an offset term in the regression equation. With one observation per individual, we will use logistic regression, where an observation is one if the outcome is in the risk interval and zero if it is in the control interval. Unlike in the unadjusted analysis, we will include an offset term to adjust for the differential risk of Kawasaki disease at the ages in the risk and comparison intervals. This offset term requires a good estimate of the natural relative incidence of Kawasaki disease by age. It will be treated in this logistic regression analysis as known with certainty, which has been shown to work well in other studies (Li et al 2015, manuscript in progress).

In a secondary analysis, we will adjust for age with conditional Poisson regression. The outcome will be the occurrence of Kawasaki disease. We will compare the risk of Kawasaki disease during the 28-day risk interval after PCV13 to the risk of Kawasaki disease during the 28-day comparison interval, adjusting for the four-week age difference between these two intervals. The risk of Kawasaki disease by week of age will be modeled as a continuous function using either polynomials or splines. The selection of the best-fitting polynomial or splines to describe the risk-by-age relationship will be done without including the risk interval in the model, to ensure integrity of the results. This method will estimate the incidence curve by age from PRISM Kawasaki disease rates in all eligible exposed or unexposed time. In the Poisson regression, the conditioning will be done on individuals, ensuring a self-controlled analysis. This means that individuals without the outcome in either the risk or the control interval are only used to estimate the incidence curve by age, while individuals with the outcome in either the risk or control interval are used to estimate both the incidence curve and the risk of Kawasaki disease associated with the vaccine.

Because the sample size to be used for the age adjustment is larger in the Holman et al. study than it is expected to be in our study population, the first method is preferable, in our view. Note that, if the incidence estimate is off by the same magnitude at all ages, for example, 10% higher than actual at all ages, it is inconsequential for a self-controlled analysis.

Study design and analysis methods are shown in Table 1.

### Cohort Poisson Regression Analysis

The second design that we will use is a cohort design with unconditional Poisson regression, including the exposed person-time from the time of licensure of PCV13 (February 2010) to the most up-to-date data, and unexposed person-time for the entire cohort from the year 2008 to the most up-to-date data. The following covariates will be included in versions of the Poisson regression model before settling on the most parsimonious and explanatory model: vaccination risk window (yes/no), age in weeks modeled as a continuous variable, sex, and calendar year as a continuous variable, and Data Partner. It is not feasible to include race/ethnicity as a covariate in this analysis as that information is not widely available in the Sentinel data. Exposed person-time will be the 1-28 days after PCV13 vaccination, while unexposed time will be the time outside of the 7 days before through the 42 days after vaccination with either PCV13 or PCV7. (We exclude the 7 days prior to vaccination from unexposed time in order to control for the healthy vaccinee effect and similar effects that could result from dependency of vaccination on one’s health condition in the week prior.) We will include unexposed person-time from children who are not vaccinated with PCV7 or PCV13 but have at least one documented healthcare visit. A polynomial risk function will be used to refine estimates of background rates by week of age during the first 1.5 years of life. We will systematically try at least linear, quadratic, cubic, fourth-order, and fifth-order functions, without exposure in the model (to blind ourselves to the effect of vaccination), and select the function to include in the final model based on the log-likelihood ratio, p-value, Akaike information criterion (AIC), and biologic plausibility. If we cannot find a well-fitting polynomial function, we will try splines instead.

Dose PCV13 Kawasaki disease

unexposed exposed unexposed

Figure 5. Cohort design to evaluate the incidence rate ratios comparing rates in the exposed and unexposed intervals

In addition to the results from the Poisson regression, the final report will include the total number of observed and expected cases during the exposed time, summed over all the data providers. Stratified by dose and age in weeks, but summed over all data providers, we will also present a table with the number of cases during exposed time, the number of cases during unexposed time, the number of exposed person-days and the number of unexposed person-days. In a secondary cohort analysis, we will consider the exposed interval as 1-42 days after PCV13 vaccination and unexposed time as the time outside of the 7 days before vaccination with either PCV13 or PCV7 through the 42 days after vaccination. We include this risk interval to further explore the finding in a study by Abrams et al. suggesting that vaccination was associated with a transient decrease in Kawasaki disease incidence.^28^

Table 1. Study designs and analyses. The primary analysis is the self-controlled logistic regression with age adjustment using an incidence curve from the literature.

| **Study designs and analyses** | | | |
| --- | --- | --- | --- |
| Self-controlled | | | Cohort |
| Logistic regression | | Conditional Poisson regression | Unconditional Poisson regression |
| **Primary analysis:**  Age adjustment using offset term based on incidence curve from literature | No age adjustment | Age adjustment internal, based on polynomial risk function from study population | Age adjustment internal, using polynomial or spline risk function |

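### The cohort Poisson model keeps covariates for parsimony and fit, so calendar year, Data Partner or sex may be dropped, and the exposure blinding used for the age function is not extended to that choice

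*Protocol*

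**What the plan says.** Protocol IV.E.4 (Cohort Poisson Regression Analysis) sets the rule for the cohort model: covariates go into several versions of it "before settling on the most parsimonious and explanatory model: vaccination risk window (yes/no), age in weeks modeled as a continuous variable, sex". The full list is "vaccination risk window (yes/no), age in weeks modeled as a continuous variable, sex, and calendar year as a continuous variable, and Data Partner". The exposure term is thus one of the listed covariates. None is marked as mandatory, and no criterion or threshold is given for choosing between versions.

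The same section handles the shape of the age curve differently. Polynomials of increasing order are fitted "without exposure in the model (to blind ourselves to the effect of vaccination), and select the function to include in the final model", and the choice is made "based on the log-likelihood ratio, p-value, Akaike information criterion (AIC), and biologic plausibility". Section IV.E.3 applies the same principle to the conditional Poisson analysis, where selection of the age curve "will be done without including the risk interval in the model, to ensure integrity of the results".

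Section IV.E.4 also fixes the time base: exposed person-time runs from PCV13 licensure in February 2010, and unexposed person-time from 2008. On race/ethnicity it states: "It is not feasible to include race/ethnicity as a covariate in this analysis". Table 1 secures age adjustment for the cohort model but mentions no other covariate.

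**The concern.** The cohort analysis estimates the effect of a vaccine, so its covariates are there to control confounding. A covariate that predicts the outcome only weakly can be dropped for parsimony and still shift the exposure estimate, if it is strongly related to exposure. Calendar year fits that description: the stretch from 2008 to early 2010 contains only unexposed time, so a secular trend in incidence, diagnosis or coding would be attributed to the vaccine once year is out of the model. Data Partner and sex can be dropped under the same rule.

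The protocol recognises the hazard of model selection and guards against it for the age function, but the guard is not stated for the remaining covariates.

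What is at stake is a supporting result that still carries weight. Section IV.E.2 places the cohort design among the hypothesis-testing analyses and expects it to have higher power than the self-controlled design. Under IV.E.7, a significant elevation in any analysis triggers data checks and a temporal scan.

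**Working it through.** **The plan's own figure.** The protocol gives no number for the cohort model. The nearest is the self-controlled power in Table 2 (IV.E.6), which supplies the dose count and background rate used below.

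- Exposed person-years: 3,388,104 × 28/365.25 = 259,731.
- Expected cases per 28-day window: 259,731 × 8.7/100,000 = 22.6.
- One-sided Wald power at RR 1.9: Φ(ln 1.9 / √(1/22.6 + 1/(1.9 × 22.6)) − 1.645) = 79.5%, against 80.0% stated.

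The inputs are therefore read correctly. The point itself does not depend on this figure.

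**Direct bias if calendar year is left out.** Assume eight calendar years (2008–2015), unexposed time spread evenly over all eight, exposed time spread evenly over the last six, a log-linear background trend of b per year centred at mid-period, and no vaccine effect. The ratio that a model without year targets is

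mean of exp(b·t) over the last six years ÷ mean of exp(b·t) over all eight.

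| b per year | Exposed mean | Unexposed mean | Apparent ratio (truth 1) |
|---|---|---|---|
| +0.05 | 1.055 | 1.007 | 1.05 |
| −0.05 | 0.955 | 1.007 | 0.95 |
| +0.10 | 1.121 | 1.026 | 1.09 |

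The bias takes the direction of the trend and is about one year's worth of it.

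**What selection does to the test.** A Monte Carlo Poisson regression was run with a true RR of 1. From the protocol: the dose count, the background rate, six Data Partners and exposed time from 2010 only. Assumed: unexposed person-time six times exposed (about 136 expected unexposed cases), the trend, a male-to-female rate ratio of 1.6 (within the 1.5–1.7 range in II.C), age already handled, and no Data Partner effect. The exposure term was in every version. All subsets of year, sex and Data Partner were fitted, and one was kept by AIC or BIC. There were 4,000 runs per setting, so the simulation error is √(0.05 × 0.95/4000) ≈ 0.35 points.

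| b per year | Rule | Year dropped | One-sided rejection, all kept | After selection |
|---|---|---|---|---|
| 0 | AIC | 84% | 4.9% | 5.0% |
| 0 | BIC | 98% | 4.3% | 4.4% |
| +0.03 | AIC | 71% | 4.9% | 5.4% |
| +0.03 | BIC | 92% | 5.9% | 6.8% |
| +0.05 | AIC | 51% | 5.4% | 6.4% |
| +0.05 | BIC | 81% | 5.4% | 7.5% |
| +0.10 | AIC | 8% | 5.3% | 5.7% |
| +0.10 | BIC | 28% | 5.8% | 7.0% |
| −0.05 | AIC | 50% | 5.4% | 4.9% |
| −0.05 | BIC | 80% | 5.5% | 4.4% |

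At b = +0.05 the excess over the fixed model is 6.4 − 5.4 = 1.0 point (AIC) or 7.5 − 5.4 = 2.1 points (BIC). At b = 0 it is 0.1 point. At b = −0.05 rejection falls, and the geometric mean RR is 0.97 (AIC) or 0.96 (BIC), against 0.98 and 0.99 with all covariates kept. Selection alone thus lowers it by roughly 1% to 3%.

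**The case against.** The strongest reply is that the list of candidate covariates is closed, that the exact criterion is the kind of detail a statistical analysis plan supplies, and that such a plan may exist. The criterion could indeed be set there. But the protocol is not silent here: it states a rule for keeping covariates, and that rule lets a confounder go.

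A second reply is that the analysis is not primary, and that the protocol openly says its confounding control is weaker. This stands and limits the weight of the point. The primary self-controlled analysis controls fixed factors such as sex and race/ethnicity by design.

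A third reply is that vaccinated children contribute both exposed and unexposed time, so the mix of Data Partner and sex is partly balanced. This also stands, although unvaccinated children and time before 2010 are not balanced in that way. Calendar year, not Data Partner, is therefore the main worry.

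A reader might infer more than the text supports:

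- **That analysts will choose covariates while looking at the vaccine estimate.** The protocol does not say so. The exposure term is in the list, and blinding is stated only for the age function. Had the most significant version been kept in the simulation, rejection would have been 8.5% to 8.7% at b = +0.05 and about 12% at b = +0.10, but the stated rule is parsimony and explanatory power, not significance.
- **That the reported interval will ignore the selection.** No allowance is described, but that is silence, and a plan not shown could add one.
- **That the incidence contrast between racial/ethnic groups in II.C, or the number of possible model versions, measures the bias.** Neither does. The first says nothing about differences between Data Partners, and the second only counts models.

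**Conclusion.** The point holds as a weakness in the specification of a non-primary analysis. As written, the rule allows calendar year, Data Partner or sex to be dropped for parsimony, and the protocol's own safeguard against exposure-driven selection is not extended to that choice.

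The consequence is conditional. If background rates trend over time, the incidence rate ratio could be biased in the direction of the trend. If they rise, the p-value could be anti-conservative, by about 1 to 2 points on a 5% one-sided test under an assumed rise of about 5% per year. With no trend the effect is negligible, and with a falling trend the test does not over-reject. These sizes rest on an assumed trend, an assumed person-time ratio and mechanical AIC or BIC selection, none of which the protocol specifies for this step. The effect of dropping Data Partner was not measured. The change is worth making because it is cheap, not because the expected error is large.

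**What to change.** Replace the selection sentence in IV.E.4 with one pre-specified cohort model: the risk window, the age function chosen without exposure as already planned, sex, calendar year and Data Partner, all retained regardless of fit. Report reduced models only as sensitivity analyses. If any covariate selection is kept, state its criterion and carry it out with the exposure term out of the model, as is done for the age function.

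The cost is a wording change and about 7 degrees of freedom for the last three terms (sex 1, continuous calendar year 1, six Data Partners 5). It needs no new data and leaves the primary analysis unchanged.

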In 2000, FDA licensed the first pneumococcal conjugate vaccine, 7-valent pneumococcal vaccine (PCV7) (Prevnar; Wyeth), for use in infants and young children. PCV7 protected against strains of *Streptococcus pneumoniae* that most commonly caused illness among children in the U.S. Subsequently, inclusion of PCV7 in the recommended children immunization program resulted in decreased rates of invasive pneumococcal disease.[^8^](#_ENREF_8) The CDC reported that rates of PCV7-type invasive pneumococcal disease in children under 5 years of age dropped from 80 cases per 100,000 to less than 1 case per 100,000 following the implementation of the PCV7 vaccine.[^9^](#_ENREF_9) FDA licensed a second vaccine, PCV13 on February 24^th^, 2010 to protect against 6 additional serotypes that accounted for much of the invasive pneumococcal disease in young children not covered by the PCV7 vaccine.[^10^](#_ENREF_10) The Advisory Committee on Immunization Practices (ACIP) recommended PCV13 for use as a 4-dose vaccination series, administered at 2, 4, 6 and 12-15 months of age, similar to the PCV7 vaccine recommendations. Full implementation of the transition from PCV7 to PCV13 came into effect in March 2010 with supplies of PCV13 available to the public sector that month as shown in Figure 1.[^11^](#_ENREF_11) By July 2010, Pfizer reported that >90% of its private shipments of pneumococcal conjugate vaccines were for PCV13.[^11^](#_ENREF_11) Children previously vaccinated with PCV7 finished their remaining vaccinations with PCV13. A dose of PCV13 was recommended by ACIP for children 14-59 months of age who had completed the 4-dose vaccination series with PCV7, and children with specified underlying medical conditions receive a 5^th^ dose until 71 months of age.[^10^](#_ENREF_10)

[figure not shown]

Figure 1. “Pneumococcal conjugate vaccine doses administered to children aged 0 through 59 months, by vaccine type and week --- Immunization Information System sentinel sites, United States, March 7--August 21, 2010.” [^11^](#_ENREF_11)

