# Methods

## Study Population and Data Sources

Six Data Partners will participate in this evaluation, and all will have data available from 2008 until the most recent data refresh. The study population will include infants and children from birth until 23.99 months of age who were members of the participating Data Partners during 2008 to 2015 and who meet the other enrollment criteria. When the data analysis programs are run, we will use the most up-to-date information from each Data Partner.

Infants and children meeting the following criteria will be included in the evaluation:

- Exposed to at least 1 dose of PCV vaccine and continuously enrolled in the Data Partner from birth through at least 84 days (risk and control intervals (56 days) plus 28 days to account for delays in symptom onset and Kawasaki disease diagnosis coding) after their first dose of PCV vaccine.
- Unexposed to PCV vaccine and continuously enrolled in the Data Partner from birth through at least 144 days of age (60 days, the time that many infants would receive dose 1, plus 84 days), with at least one documented healthcare visit in any setting between 14 and 150 days.

Gaps of up to 45 days between birth and enrollment will be allowed. For both exposed and unexposed categories of subjects, continuously enrolled person-time through a maximum age of 23.99 months will be included in the analyses, with the following proviso:

- If an infant in the exposed category has incomplete person-time during *0-84 days after Dose 2* of PCV vaccine, his/her person-time on and after the day of that vaccination will be excluded;
- If a child in the exposed category has incomplete person-time during *0-98 days after Dose 3 or 4* of PCV vaccine, his/her person-time on and after the day of that vaccination will be excluded.

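### The non-primary cohort models pool never-vaccinated children into the reference with no term separating them, so a difference in their background rate biases the cohort rate ratio, by a probably modest amount

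*Protocol*

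**What the plan says.** Protocol, Cohort Poisson Regression Analysis, defines the two kinds of time. On the exposed side it states: "Exposed person-time will be the 1-28 days after PCV13 vaccination". For the reference it sets a wider exclusion around every dose: "unexposed time will be the time outside of the 7 days before through the 42 days after vaccination with either PCV13 or PCV7". It then adds children with no PCV dose to the reference: "We will include unexposed person-time from children who are not vaccinated with PCV7 or PCV13 but have at least one documented healthcare visit". The candidate covariates are "vaccination risk window (yes/no), age in weeks modeled as a continuous variable, sex, and calendar year as a continuous variable, and Data Partner". The same section says that race/ethnicity cannot be included. A second cohort model uses days 1-42 as exposed time. No vaccinated-only cohort analysis is named.

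Study Population and Data Sources already sorts children into those with at least one PCV dose and those with none. The latter must have a healthcare visit between 14 and 150 days.

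Overview of hypothesis-testing analyses concedes the risk: "If there are differences among racial/ethnic groups in vaccine coverage and timing, an important potential confounder in the cohort design will be race/ethnicity". The Kawasaki Disease section gives 32.5 per 100,000 in children of Asian and Pacific Island descent against 9.1 in non-Hispanic whites, both under 5 years. Table 1 makes the self-controlled logistic regression the primary analysis.

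**The concern.** All exposed time comes from vaccinated children, but the reference mixes their own unexposed time with that of never-vaccinated children. If the two groups differ in background rate, through race mix, care seeking or incomplete capture of doses in claims, the difference enters the rate ratio for the risk window. No listed covariate can absorb it.

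The exclusion around each dose adds to this. A child vaccinated exactly on schedule contributes no reference day at any age at which that child is exposed. The never-vaccinated therefore weigh more at post-dose ages than their number suggests.

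The cohort result has consequences although it is not primary. Under Evaluation of Elevated Risks, a significant elevation in any analysis triggers follow-up. The 1-42 day model is meant to explore a reported transient decrease after vaccination, and a higher background rate in never-vaccinated children would produce a rate ratio below 1 with no vaccine effect at all.

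**Working it through.** **The plan's own figures.** None is given for the cohort model. The stated power for the self-controlled design can be reproduced. Control-window cases are 3,388,104 × 28/365.25 × 8.7/100,000 = 22.6. At RR 1.9, n = 22.6 × 2.9 = 65.5 and p = 1.9/2.9 = 0.655. Power = Φ(√(65.5 × 0.655 × 0.345) × ln 1.9 − 1.645) = 79.5%, against 80.0% in Table 2. This says nothing about the cohort model.

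**Reference time of an on-schedule child.** Doses are "administered at 2, 4, 6 and 12-15 months of age", and "continuously enrolled person-time through a maximum age of 23.99 months will be included in the analyses", about 730 days. Days -7 to 42 are 50 days per dose. Reference time is 730 − 4 × 50 = 530 days and exposed time is 4 × 28 = 112 days, with no age in common. With doses at days 61, 122 and 183 (assumed), only 11 reference days remain between successive doses (104-114 and 165-175).

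**Overall share.** With a fraction f never vaccinated, the share is f × 730 / [f × 730 + (1 − f) × 530]. This gives 6.8% for f = 5% and 13.3% for f = 10%.

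**Share at exposed ages.** This depends on the spread of dose timing, which is not stated. For f = 5% it is 11% with loose timing, 24% with moderate, 43% with tight, and 100% if every dose is exactly on time. It is concentrated after doses 1-3 (29% with moderate timing) rather than dose 4 (7%). Across f = 1-20% with some spread in timing it runs from 2.5% to 68%.

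**Effect on the rate ratio.** Expected-count Poisson fits by week of age, true RR 1, fifth-order age polynomial, moderate timing. Age curve, timing spread, f and the rate multiplier are all assumptions.

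| Never vaccinated | Share of reference, all ages | Share at exposed ages | Their rate ×0.5 | ×0.8 | ×1.25 | ×2.0 |
|---|---|---|---|---|---|---|
| 1% | 1.3% | 7.9% | 1.010 | 1.004 | 0.995 | 0.980 |
| 5% | 6.5% | 23.7% | 1.051 | 1.020 | 0.976 | 0.910 |
| 10% | 12.8% | 35.5% | 1.102 | 1.038 | 0.955 | 0.841 |
| 20% | 24.9% | 51.2% | 1.201 | 1.072 | 0.921 | 0.744 |

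With an ever/never-vaccinated term, every cell returns 1.00.

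**Effective weight.** These results follow RR ≈ 1/[1 + w(m − 1)], where m is the rate multiplier and w the effective weight of the never-vaccinated. Solving at m = 0.5 gives w = (1 − 1/1.051)/0.5 = 0.097 for f = 5% and (1 − 1/1.102)/0.5 = 0.185 for f = 10%. Both lie between the overall share and the share at exposed ages, because the smooth age curve borrows from all weeks.

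**A 30% difference.** For f = 5%, the formula gives 1/(1 − 0.097 × 0.3) = 1.03 and 1/(1 + 0.097 × 0.3) = 0.97. For f = 10%, it gives 1/(1 − 0.185 × 0.3) = 1.06 and 1/(1 + 0.185 × 0.3) = 0.95. Direct fits under other assumed age curves and timing gave 1.02-1.03 and 0.96-0.97 at 5%, and 1.05-1.09 and 0.91-0.95 at 10-15%. With the term they returned 0.99-1.00.

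**Sensitivity to timing and age model.** At f = 5% and multipliers 0.5 / 2.0, the polynomial fit gives 1.044 / 0.921 with loose timing and 1.056 / 0.903 with tight timing, so timing changes the share far more than the bias. With week-of-age categories and tight timing the values are 1.103 / 0.836. A flexible spline, the protocol's fallback, could move towards these.

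**Race example.** The ratio 32.5/9.1 is 3.57. If the high-rate group made up 3% of never-vaccinated and 10% of vaccinated children (assumed), the rate multiplier would be (1 + 0.03 × 2.57)/(1 + 0.10 × 2.57) = 0.86. The fitted RR is then 1.00, 1.02 and 1.03 at 5%, 10% and 15% never vaccinated.

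**The case against.** - **Disclosure and mitigation.** The protocol says that the cohort design controls fixed confounders less well, and it makes the self-controlled analysis primary for that reason. It requires an early healthcare visit from unexposed children and seeks immunization records for cases without PCV history. All of this stands, but none of it separates the two groups in the model. The record check is described for cases only. If the matching person-time of non-cases is not corrected as well, the apparent rate in never-vaccinated children falls and the rate ratio is pushed upward.
- **Size.** The standard error of the log rate ratio is about 0.21 at 200 cases, the protocol's cap on chart reviews. A 95% interval then spans a factor of exp(1.96 × 0.21) = 1.51 either way. A rate ratio of 0.91 is |ln 0.91|/0.21 = 0.45 standard errors from 1. This stands, and it keeps the point below a threat to the study's conclusion.
- **A large share.** A reader might infer that the reference at post-dose ages is mostly never-vaccinated children. The documents do not support this. They give neither coverage nor dose-timing spread, and the smooth age function means the comparison is not confined to those ages.
- **A complete cure.** A reader might also infer that the added term removes between-child confounding. The return to 1.00 is partly built in, because the fits impose a constant multiplier and then estimate it. Differences between on-time and late vaccinees remain.
- **Left to a SAP.** The covariate list and the composition of the reference are fixed in this protocol, so the point can be raised here.

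**Conclusion.** The point holds in a limited form. The cohort models include "children who are not vaccinated with PCV7 or PCV13" in the reference without separating them, and the exclusion around each dose gives them disproportionate weight at post-dose ages. A lower background rate in these children biases the rate ratio upward, and a higher rate biases it downward. With a 30% difference the bias is about 2-4% at 5% never vaccinated and about 5-9% at 10-15%. It is negligible at 1% and reaches 0.84 for a doubled rate at 10%.

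These sizes rest on assumed coverage, dose timing, age curve and rate differences, because the protocol states none of them for this population. The primary self-controlled result is untouched. This is an avoidable bias of uncertain, probably modest size in a supporting analysis, worth correcting because the correction is specific and nearly free.

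**What to change.** Add the category that Study Population and Data Sources already defines, any recorded PCV dose (yes/no), to both cohort Poisson models (1-28 and 1-42 days). Keep it as a fixed term, outside the search for the most parsimonious model. Never-vaccinated children then still inform the age, calendar-year and Data Partner effects, while the vaccine estimate rests on exposed against unexposed time among vaccinated children. Alternatively, keep the present model and report a vaccinated-only cohort fit beside it.

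State in the protocol that this removes only the ever/never difference and leaves confounding by dose timing among vaccinated children. Report the share of never-vaccinated children, so that readers can judge the size of the adjustment.

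The cost is one covariate already held for every child and a standard error of the log rate ratio larger by roughly 1-4%, for example 0.210 to 0.216 at 200 cases (0.216/0.210 = 1.03).
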